## **Inferential statistics**

The mean and 95% confidence interval based on t-distribution or Wald method will be the output. For variables with normality of the residuals not holding, the mean and 95% confidence interval based on t-distribution or Wald method will be calculated using the natural logarithm scale, and the output will be values converted to the original scale by inverse logarithm transformation.

## **Analysis using linear models and mixed-effect models for repeated measures (MMRM)**

The estimation results of group effects (estimated values, 95% confidence intervals based on t-distribution or Wald method), and *P* values of the hypothesis test for the null hypothesis of "no group effect" will be the output. The significance level was set at a two-sided *P* value of < 0.05. For variables with normality of the residuals not holding, the analysis is performed using the natural logarithm scale, and the outputs will be the estimates and 95% confidence intervals after being converted to the original scale using an inverse logarithmic transformation.

## **Frequency counting**

The number and proportion (%) of the cases will be the output. If needed, the 95% confidence interval of the proportion of cases will be calculated using the Clopper–Pearson method.

## **Addressing multiplicity of tests**

In this study, the evaluation of treatment efficacy will be based on the primary analysis of the primary endpoint targeting the full analysis set (FAS). Multiplicity adjustments will not be performed for supplementary analyses of the primary endpoint, analyses of the per-protocol set (PPS), or analyses of secondary endpoints. However, as an exception, for proteomics analyses, methods to address multiplicity within the proteomics analysis will be specified separately.

# **Statistical** **analysis**

## **Patient classification**

The following numbers of cases will be verified with those with consent obtained:

- Number of cases with consent obtained
- Number of registered cases
- Number of unregistered cases
- Number of allocated cases
- Number of unallocated cases
- Number of SS cases in each treatment group
- Number of cases excluded from SS in each treatment group
- Number of FAS cases in each treatment group
- Number of cases excluded from the FAS in each treatment group
- Number of PPS cases in each treatment group
- Number of cases excluded from the PPS in each treatment group
- Number of patients completing the 24-week follow-up in each treatment group in the FAS
- Number of patients not completing the 24-week follow-up in each treatment group in the FAS
- Number of patients completing 24 weeks of treatment in each treatment group in the FAS
- Number of patients not completing 24 weeks of treatment in each treatment group in the FAS

For unallocated cases, the reasons for no allocation will be tabulated. For allocated patients discontinuing before or after the treatment initiation, the reasons for their exclusion will be tabulated by treatment group. For allocated patients excluded from the SS, patients in the SS excluded from the FAS, patients in the FAS excluded from the PPS, and the reasons for their exclusion will be tabulated by treatment group. For patients in each treatment group not completing the 24-week follow-up or 24-week treatment, the reasons for their exclusion will be tabulated.

## **Demographic and clinical characteristics**

For each population (randomized, FAS, PPS, SS), descriptive statistics and frequency tabulations of the following items will be performed for the entire population and for each treatment group.

- Age (at the time of registration)
- eGFR (at the time of registration)
- UACR (at the time of registration)
- HbA1c (at time of registration)
- Serum potassium (at time of registration)
- LVEF (at the time of enrollment)
- Duration of diabetes (at the time of enrollment)
- Height (baseline)
- Weight (baseline)
- BMI (baseline)
- Clinic blood pressure (systolic and diastolic) (baseline)
- Clinic pulse (baseline)
- Home blood pressure (systolic and diastolic) (baseline)
- Home pulse (baseline)
- Gender (at the time of registration)
- Use of SGLT2 inhibitors (at time of registration)
- Presence or absence of complications or history of comorbidities (hypertension, dyslipidemia, ischemic heart disease, stroke, lower limb arteriosclerosis obliterans, heart failure) (at the time of registration)
- Primary underlying disease of chronic kidney disease (diabetic nephropathy, non-diabetic nephropathy: chronic glomerulonephritis, nephrosclerosis, polycystic kidney disease, collagen disease-related nephropathy, others) (at the time of registration)

## **Description of the medication adherence for the study treatment**

For the SS and FAS, descriptive statistics and frequency estimation will be conducted for medication adherence for the study treatment by treatment group and study visit.

## **Concomitant medication use description**

Descriptive statistics and frequency estimation will be conducted for concomitant medication use by treatment group and study visit for the FAS. The concomitant medications that will be assessed include ACE inhibitors, ARBs, ARNIs, β-blockers, calcium antagonists, diuretics, statins, insulin, metformin, SGLT2 inhibitors, GLP-1 receptor agonists, DPP-4 inhibitors, iron preparations, ESAs, HIF-PH inhibitors, and hyperkalemia medications.

## **Analysis of the primary endpoint**

The following analysis will be performed on the FAS as the primary analysis. Furthermore, an analysis will be conducted using the PPS to confirm the robustness of the results.

1. Descriptive statistics calculations will be conducted, and histograms will be plotted to assess CAVI and its participant-level change and proportional change by treatment group and study visit. Inferential statistics calculations will be used to estimate CAVI mean and change, and geometric mean and proportional change at population-level by treatment group and study visit.
2. As the primary analysis for the primary endpoint, change in CAVI at 24 weeks will be analyzed using a linear regression model with baseline values as covariates and allocation as fixed effects. To assess treatment effect, the between-group difference in CAVI change using the least squares mean at 24 weeks will be estimated using the placebo group as a reference. The output will be the *P* value of the test for the null hypothesis that the between-group difference in change is 0. Moreover, the presence or absence of a treatment effect will be determined using the criteria of a two-sided *P* value of < 0.05.
3. As a supplementary analysis for the primary endpoint, change in logarithmic CAVI at 24 weeks will be analyzed using a linear regression model with logarithmic baseline values as covariates and allocation as fixed effects. To assess treatment effect, the between-group ratio of the proportional change in CAVI geometric mean using the least squares mean at 24 weeks will be estimated using the placebo group as a reference. The output will be the *P* value of the test for the null hypothesis that the between-group ratio is 1.

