## Randomization procedure

Study participants will be randomly assigned using a central registration system. After confirming their eligibility, the principal investigators and co-investigators will promptly access the study’s website (EDC) and enter the required registration information. The information will be immediately verified on the EDC site, and if eligible, a patient identification number will be assigned. Then, dynamic allocation will be performed on the EDC.

Dynamic allocation to the finerenone and placebo groups will be performed using the minimization method in a 1:1 ratio with the following allocation stratification factors:

[Allocation factor]

Age at time of consent (< 70 years / ≥ 70 years)

Sex (female/male)

eGFR (< 60 mL/min/1.73 m^2^ / ≥ 60 mL/min/1.73 m^2^)*

Use of SGLT2 inhibitors at the time of consent (yes/no)

*Data obtained after obtaining consent will be prioritized; however, if such data cannot be obtained, data obtained within three months prior to obtaining consent may be used.

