## Efficacy analysis

## Efficacy analysis

1. Analysis of the primary endpoint

The change in CAVI at 24 weeks after protocol treatment initiation compared to that at baseline will be analyzed using a linear regression model with the treatment group as a fixed effect factor and baseline CAVI value as a covariate. Moreover, the mean values of both treatment groups at 24 weeks and their 95% confidence intervals, as well as the treatment effect estimated by the difference in the mean values between the treatment groups and their 95% confidence intervals will be calculated. A test will be performed against the null hypothesis such that the difference in treatment effect is 0.

1. Analysis of secondary endpoints
2. Proportional change in geometric mean of UACR at 12 and 24 weeks after protocol treatment initiation compared to that at baseline (important secondary endpoint):

The change in logarithmic UACR values from baseline to 12 and 24 weeks after the protocol treatment initiation will be analyzed using mixed-effects models for repeated measures (MMRM) with the treatment group as a fixed effect factor, baseline value and time point as covariates, and group and time point interaction. The results will be back-transformed to the original UACR scale, and the proportional change in UACR geometric mean and its 95% confidence interval for both treatment groups at 12 and 24 weeks, as well as the treatment effect estimated by the ratio of the proportional change between the treatment groups and its 95% confidence interval, will be calculated. A test will be performed against the null hypothesis such that the treatment effect ratio is 1 at each time point.

1. Proportional change in geometric mean of blood biomarkers (pentosidine) and urinary biomarkers (type IV collagen, α1-MG, β2-MG, NGAL, NAG, L-FABP creatinine ratio) at 24 weeks after the protocol treatment initiation as compared to those at baseline:

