| **2. Research contents**  **2.5. Regulations for handling study drugs (management and distribution procedures)**  **2.5.1. Centralized management of study drugs**  Both the active and placebo test drugs will be delivered to the Department of Cardiology at Saga University Hospital by Bayer Yakuhin, Ltd., where they are temporarily stored. Each bottle is assigned a different number and a correspondence table of active drug and placebo is delivered at the same time. After delivery, the Study Drug Allocation Officer will pack for each case individually while checking the correspondence table. | **2. Research contents**  **2.5. Regulations for handling study drugs (management and distribution procedures)**  **2.5.1. Centralized management of study drugs**  Both the active and placebo test drugs will be delivered to the Department of Cardiology at Saga University Hospital by Bayer Yakuhin, Ltd. After being allocated (packaged) by the Study Drug Allocation Officer, they will be stored in the Pharmacy Department at Saga University Hospital. | Description adjustment |
| **2. Research contents**  **2.5. Regulations for handling study drugs (management and distribution procedures)**  **2.5.2. Delivery of study drugs to each medical institution**  The drugs will be delivered to each participating medical institution by an independent Study Drug Management Officer in the Pharmacy Department of the Saga University Hospital. | **2. Research contents**  **2.5. Regulations for handling study drugs (management and distribution procedures)**  **2.5.2. Delivery of study drugs to each medical institution**  The drugs will be delivered to each participating medical institution by an independent Study Drug Central Manager in the Pharmacy Department of the Saga University Hospital. | Description adjustment |
| **2. Research contents**  **2.8. Randomization procedure**  [Allocation factor]  eGFR (< 60 mL/min/1.73 m^2^ / 60 mL/min/1.73 m^2^ or >)* | **2. Research contents**  **2.8. Randomization procedure**  [Allocation factor]  eGFR (< than 45 mL/min/1.73 m^2^ / 45 mL/min/1.73 m^2^ or >)* | Typo |

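### The primary CAVI model omits the four minimisation factors; to the extent that they predict CAVI change beyond baseline CAVI, its standard error is conservative and some precision is forgone

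*Combined protocol and SAP*

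**What the plan says.** Protocol, Randomization procedure: dynamic allocation "will be performed using the minimization method in a 1:1 ratio with the following allocation stratification factors". The factors are age at consent (cut at 70 years), sex, eGFR, and SGLT2-inhibitor use at consent. The printed body, which carries the version 1.1 text, cuts eGFR at 60. The version 1.2 amendment table changes this to "eGFR (< than 45 mL/min/1.73 m^2^ / 45 mL/min/1.73 m^2^ or >" and gives a typo as the reason.

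Protocol, Efficacy analysis: the change in CAVI "will be analyzed using a linear regression model with the treatment group as a fixed effect factor and baseline CAVI value as a covariate". The SAP's section on the primary endpoint analysis has this wording: "change in CAVI at 24 weeks will be analyzed using a linear regression model with baseline values as covariates and allocation as fixed effects". The two documents agree, and neither includes the allocation factors.

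The SAP's other analyses of the primary endpoint are a repeat in the per-protocol set, a log-CAVI version and a list of subgroups. Age at 70, sex, eGFR (at both 45 and 60) and SGLT2-inhibitor use appear as subgroups, but no analysis adjusts for them.

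**The concern.** Minimisation forces the arms to be alike on the four factors. If those factors predict the outcome, the treatment difference varies less from trial to trial than it would under simple randomisation. A model that leaves them out still counts their variance as residual noise. Its reported standard error is then larger than the true sampling variability, the 95% interval is too wide, and the test rejects less often than 5% under the null.

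The primary CAVI test is the one on which the SAP bases its efficacy conclusion, and the plan allows for about 45 evaluable patients per arm. Precision that could be had from data already recorded at registration is worth having.

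**Working it through.** **1. Reproduce the plan's sample size.** Inputs from the protocol's Sample size section: effect 0.6 SD, two-sided 5%, power 80%, dropout 10%.
- Normal approximation: n = 2(1.960 + 0.842)² / 0.6² = 43.6, so 44 per arm. 44 / 0.9 = 48.9, so 49 per arm, 98 in total.
- Two-sample t-test: 45 per arm. 45 / 0.9 = 50 per arm, 100 in total.

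The stated 100 is reproduced, and the calculation needs no covariate adjustment.

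**2. Size of the effect in principle.** Let R² be the share of residual variance in CAVI change, after baseline CAVI, that the four factors explain. The documents do not give it, so 0 to 0.20 is assumed. Adjustment multiplies the standard error by √(1 − R²): 0.975, 0.949 and 0.894 at R² = 0.05, 0.10 and 0.20. With perfect balance, the planned test behaves as if its critical value were 1.96 / √(1 − R²) = 2.011, 2.066 and 2.191. Its type I error is then about 4.4%, 3.9% and 2.8%.

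**3. Simulation.** Each trial has 100 patients minimised on four independent binary factors (prevalence 0.4–0.5, equal prognostic weight), 10% random dropout and an effect of 0.6 residual SD. There are 6,000 trials per setting. The documents do not give the probability of assigning the favoured arm, so 0.8 and 1.0 were both run. Each cell shows 0.8 / 1.0.

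| R² | Type I error, planned (%) | Type I error, adjusted (%) | Power, planned (%) | Power, adjusted (%) |
|---|---|---|---|---|
| 0 | 5.2 / 5.2 | 5.2 / 5.2 | 80.2 / 79.8 | 79.6 / 79.5 |
| 0.05 | 4.3 / 4.7 | 5.1 / 4.9 | 80.4 / 78.8 | 81.4 / 80.3 |
| 0.10 | 4.1 / 4.1 | 4.9 / 4.8 | 81.6 / 81.2 | 84.1 / 83.9 |
| 0.20 | 3.2 / 3.1 | 4.7 / 5.2 | 82.0 / 82.4 | 87.3 / 87.9 |

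The Monte Carlo standard error at 5% is √(0.05 × 0.95 / 6000) = 0.28 point, so the departure at R² = 0.05 is barely distinguishable from nominal. The mechanism shows in the standard errors (0.8 setting). At R² = 0.10 the planned model reports 0.212 on average while its estimates vary with SD 0.202; at 0.20 the figures are 0.212 and 0.194.

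**4. Where R² might lie: age only.** The protocol's figures are 0.5 CAVI per 10 years and an SD of about 1.5. Assume an age SD of 10 years, the same age gradient at both visits, and a baseline/week-24 correlation ρ of 0.5 to 0.7. The correlation of age with CAVI is r = 0.05 × 10 / 1.5 = 0.333, and

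R² = [r² / (1 − r²)] × (1 − ρ) / (1 + ρ) = 0.125 × (1 − ρ) / (1 + ρ).

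This gives 0.042 at ρ = 0.5 and 0.022 at ρ = 0.7. Splitting age near its median lowers these to about 0.025 and 0.01. The documents offer no figure for sex, eGFR or SGLT2-inhibitor use.

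**5. The other reading of 0.6 SD.** If it means 0.6 × 1.5 = 0.9 CAVI units against the cross-sectional SD, baseline adjustment alone leaves a residual SD of 1.5√(1 − ρ²) = 1.299 or 1.071 at ρ = 0.5 or 0.7. Power is then already about 91% or 98%, and further adjustment has less to add.

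**The case against.** The strongest reply is that nothing in the documents shows the factors to be prognostic for CAVI change once baseline CAVI is in the model. The links the protocol cites, with age and with renal function, concern the level of CAVI. A gradient of 0.5 per decade amounts to 0.05 × 24/52 = 0.023 units over the trial, and baseline CAVI already carries much of what age and eGFR say about level. If R² is zero, adjustment costs about half a power point. The sample size assumed no covariates, and the planned model delivers roughly its 80% in every setting. This all stands, and it is why the point is conditional.

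A reader might infer that the standard error is definitely too large and that power is definitely lost, or that the confirmatory test is flawed. The documents support neither. The first needs an R² they do not supply, and the age figure points to the lower end of the range. The second fails because omission causes no bias and no excess of false positives. Any loss is relative to an adjusted model, not to the plan.

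What the objection does not remove is the asymmetry. The downside of adjusting is about half a point, the upside is several points if the factors matter, and choosing them for balance suggests that they were thought to matter.

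**Conclusion.** The point holds as an efficiency improvement. The primary model omits the factors on which allocation was balanced, and no planned analysis includes them. To the extent that they predict CAVI change beyond baseline CAVI, the planned interval and P value are conservative. Adjustment changes power by about −0.5 point at R² = 0, +1 at 0.05, +2.5 to 3 at 0.10 and +5 to 6 at 0.20. The planned model's power stays at about 79–82% over that range.

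These sizes rest on an assumed R², independent and equally weighted binary factors, random dropout, and 0.6 SD read as residual SD. An R² of 0.20 is the top of the assumed range, not an expectation drawn from the documents. No calculation was made for the UACR or biomarker models, so the point is confined to CAVI.

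**What to change.** Add the four minimisation factors to the primary CAVI model in one prespecified form, namely the categories used by the allocation system: age below 70 or 70 and over, sex, eGFR at the cut actually used, and SGLT2-inhibitor use yes or no. Keep the baseline-only model as a supportive analysis. State in the SAP which eGFR cut the system applied, since the printed body has 60 and the version 1.2 amendment has 45.

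The protocol fixes the model, and the SAP declares no changes from the protocol. The protocol's Analysis method section requires both documents to be revised when an SAP change alters the protocol, and protocol revisions go to the certified review board. The change must be made before unblinding. If it is made later, report the adjusted model as a labelled sensitivity analysis; the supplementary tables supplied with these documents already show results by arm.

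The cost is four degrees of freedom and a small revision of protocol and SAP. No new data are needed, because all four factors are recorded at registration.

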# **Statistical analysis**

## Sample size

100 cases (Finerenone group, 50 cases; placebo group, 50 cases)

Rationale for sample size determination

During the research plan formulation, the clinical evidence on the effects of finerenone on surrogate markers, including vascular stiffness and biomarkers in patients with CKD complicated by type 2 diabetes, was limited. Therefore, the study sample size was set based on the results of two clinical trials: one that examined the effects of a drug of the same type as finerenone on these surrogate markers and another that examined the effects of a drug of a different type on surrogate markers similar to those in this study.

　First, a clinical trial using eplerenone, a different MRA, reported in 2021 (MIRAD: Mineralocorticoid Receptor Antagonists in Type 2 Diabetes) (1) revealed that administration of eplerenone for 26 weeks significantly improved the levels of surrogate markers associated with heart disease in patients with type 2 diabetes compared to that by placebo. The total number of participants analyzed in the study was 104, and although the participants and endpoints were different from those in this study, the effectiveness of MRA on surrogate markers related to cardiac and renal disease may be verified with a similar number of cases.

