　Next, in a subanalysis of the EMPA-TROPISM trial assessing patients with HFrEF (2), after six months of administration of the SGLT2 inhibitor empagliflozin, the change in vascular stiffness assessed by aortic pulse wave velocity was –0.58 cm/s (–0.36 SD) in the empagliflozin group and +0.60 cm/s (+0.60 SD) in the placebo group, demonstrating a significant improvement with empagliflozin (estimated effect size is approximately –0.36 SD–0.60 SD = –0.96 SD), and at the same time, proteomic analysis revealed a reduction in some inflammatory biomarkers. Moreover, in the PROTECT trial (jRCT1071220089) assessing patients with type 2 diabetes, although not limited to patients with CKD, the average CAVI value was approximately 9 with an SD of approximately 1.5 (unpublished data). Using these values, –0.6SD approximately yields a CAVI of –1; thus, in this study, the CAVI value of approximately 9 is expected to lower by approximately 1. In studies focusing on patients with diabetes and the general population (3,4), the CAVI value increased by 0.5 with approximately 10 years of aging; thus, lowering the CAVI by 1 point is equivalent to delaying the progression of arterial stiffness by approximately 20 years, and is considered to be clinically significant.

　Although no studies have directly compared the clinical effects of finerenone and empagliflozin, based on previous studies, if we assume that finerenone will improve vascular stiffness similar to that by empagliflozin as observed in the EMPA-TROPISM trial, we conservatively estimated that the CAVI in SD units from baseline to 24 weeks after treatment initiation would be reduced by > –0.6 (63% of the effect detected in the EMPA-TROPISM trial, calculated as –0.96 × 0.63 = –0.6) in the finerenone group compared to that in the placebo group, and set the significance level at 5% on both sides, power at 80%, and dropout rate at 10%. Thus, the minimum number of cases required to detect a significant difference between the two groups was set at 100 (50 in each group).

References:

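### The SAP lets a non-significant P value settle that finerenone has no effect on CAVI, which a test against zero cannot show

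*Combined protocol and SAP*

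**What the plan says.** The SAP's 'Analysis of the primary endpoint', item 2, specifies a linear regression of the 24-week change in CAVI on allocation and baseline CAVI, with a test of zero between-group difference. It then adds the decision rule: "Moreover, the presence or absence of a treatment effect will be determined using the criteria of a two-sided" P value below 0.05.

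The SAP's 'Addressing multiplicity of tests' gives that rule its weight, stating that "the evaluation of treatment efficacy will be based on the primary analysis of the primary endpoint" in the FAS. This is the rule for the trial's main conclusion.

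The protocol's 'Efficacy analysis' is more restrained. It commits to the group means, the between-group difference, their 95% confidence intervals and a test against 0, and does not speak of determining absence. The SAP's section on linear models and MMRM also lists the interval as an output. Neither document states an equivalence margin, or any rule by which the interval supports a negative conclusion.

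**The concern.** A test against a zero difference is asymmetric. A small P value is evidence against zero. A large one is compatible with no effect, and also with a useful effect estimated too imprecisely. A rule that reads the second outcome as absence goes beyond what the test can support.

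This matters here because the question is one of mechanism. The protocol's background proposes that finerenone's benefit may act partly through vascular stiffness. Under the rule as written, a non-significant result would count as evidence against that mechanism, even where the interval still contained the effect the trial was designed to detect. The trial was sized to detect one effect with 80% power. It was not sized to rule out smaller ones.

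**Working it through.** **Inputs**

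- From the protocol's 'Sample size': between-group effect 0.6 SD, two-sided 5%, power 80%, dropout 10%, 50 per arm.
- From the same section, on scale: "the average CAVI value was approximately 9 with an SD of approximately 1.5", and "the CAVI value increased by 0.5 with approximately 10 years of aging". A 1-point reduction is described there as clinically significant.
- From the SAP's 'Handling missing data': missing values are not imputed, so dropout reduces the number analysed.

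**Step 1: reproduce the sample size.** For a two-sample t-test with n per arm and standardised effect d, power comes from the noncentral t distribution with 2n − 2 degrees of freedom and noncentrality d/√(2/n). At d = 0.6, n = 45 is the smallest size that reaches 80% (power 80.4%). Then 45/0.9 = 50 per arm, 100 in total, which matches the protocol. The normal approximation gives 44 per arm, then 49 after dropout, or 98 in total.

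**Step 2: chance of P ≥ 0.05 when an effect exists.** With n = 45, √(2/45) = 0.2108.

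| True effect (SD) | Noncentrality | P ≥ 0.05, 45 per arm | P ≥ 0.05, 50 per arm |
|---|---|---|---|
| 0.6 (planned) | 2.846 | 19.6% | 15.6% |
| 0.5 (illustration) | 2.372 | 35.0% | 30.3% |
| 0.4 (illustration) | 1.897 | 53.3% | 49.2% |
| 0.3 (illustration) | 1.423 | 70.9% | 68.2% |

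The noncentralities are for 45 per arm. Under the SAP's rule, each percentage is the chance of a verdict of absence when an effect is present.

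**Step 3: what 0.5 SD means.** On the protocol's SD of about 1.5, 0.5 × 1.5 = 0.75 points, or 0.75/0.5 × 10 = about 15 years on its ageing scale. That SD describes CAVI values, not the baseline-adjusted change.

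**Step 4: sensitivity to the SD.** The documents do not give the SD of the adjusted change, so two ranges are shown, both at 45 per arm.

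- If 0.5 SD is in unadjusted units, adjustment raises the standardised effect to 0.5/√(1 − ρ²). Assuming a correlation of 0.3 between baseline and outcome gives 0.524 and a miss rate of 30.9%. Assuming 0.5 gives 0.577 and 22.7%.
- For a true 0.5-point effect, assumed residual SDs of 0.8, 1.0, 1.2 and 1.5 give miss rates of 17%, 35%, 50% and 65%.

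**Step 5: what the interval would show.** Its half-width at 45 per arm is 1.987 × 0.2108 = 0.419 SD. A non-significant estimate lies within 0.419 SD of zero, so its lower limit can reach −2 × 0.419 = −0.838 SD. A non-significant interval can therefore still contain the planned −0.6 SD. In points, −0.838 SD is −1.26 if the residual SD is 1.5 and −0.84 if it is 1.0. Whether the 1-point benchmark is excluded thus depends on the SD observed, and the interval shows this directly while the P value does not.

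**The case against.** The strongest reply is that every trial has type II error, and that the 20% at 0.6 SD is just the complement of the 80% power openly planned. The 0.5-SD effect appears nowhere in the documents. Under any rewording, P ≥ 0.05 occurs exactly as often. All of this stands. A reader might infer that the wording causes a 35% error, or that the fix removes it. Neither follows: the percentages show how often the rule would give the wrong label, and the fix changes only the label.

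It can also be said that the phrase may be a translation of a plain binary test outcome, that the estimate and interval will be reported anyway, that the protocol's 1-point benchmark lets readers judge the interval, and that no section says a negative result will be published as no effect. That last point is right, and a reader who infers that the sponsor intends such a claim goes beyond the text. But the sentence is the only stated decision rule for the primary endpoint. Reporting an interval is not the same as giving it a role in the conclusion.

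A reader might also want a formal bound, ruling out the planned effect when the interval excludes −0.6 SD. The documents do not support that yet, because they do not say which SD converts it to points. With 0.6 × 1.5 = 0.9 points as the bound, 45 per arm and assumed residual SDs of 1.0 to 1.2, a true 0.5-point effect would give P ≥ 0.05 together with exclusion of the bound in about 34% of trials. Such an exclusion would be correct, since 0.5 is smaller than 0.9, but it could easily be misread as no effect.

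**Conclusion.** The point holds as a fault in the decision rule, not in the sample size or the model. P ≥ 0.05 cannot establish absence, and the SAP says it will. At the planned effect and 45 evaluable per arm, about one trial in five would receive that label wrongly. The illustrative 0.5-SD figure is 35%, or 30% with 50 per arm, and lower if baseline adjustment reduces the residual SD (31% to 23% under assumed correlations of 0.3 to 0.5).

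These figures assume 1:1 arms and normal errors. Apart from the adjusted range, they also take the SD unit to be that of the analysed quantity, as the sample-size calculation does. The logical point needs none of these assumptions. No estimate, interval or P value changes. What changes is what the trial may conclude from a non-significant result, so the plan should be amended.

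**What to change.** In the SAP's 'Analysis of the primary endpoint', item 2, delete *or absence* and replace the sentence with:

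> A two-sided P < 0.05 will be taken as evidence of a treatment effect. P ≥ 0.05 will be reported as effect not demonstrated and interpreted through the 95% confidence interval for the between-group difference in CAVI points, including whether it excludes the reduction of about 1 point that the protocol calls clinically significant.

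Excluding 1 point should not be read as absence of smaller effects. If the residual SD is below about 1/0.838 = 1.19 points, every non-significant interval at 45 per arm excludes 1 point, so the full interval has to be described.

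The cost is a sentence of SAP text, with no extra patients, data or computation, since the interval is already an output. The downside is that some negative results must be called inconclusive.
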